### Timetable

The timetable and visit plan is outlined in Fig. 1.

**Fig. 1 Fig1:**
[figure not shown]
Visit plan. Patients will be followed for 5 years after the intervention. AE, adverse event; ASA, American Society of Anesthesiologists; CT, computed tomography; d, day; intra-OP, intraoperative; m, month; MR imaging, magnetic resonance imaging; QST, quantitative sensory testing; pre-OP, preoperative; SAE, severe adverse event; V, visit; VAS, visual analogue scale

### Investigational groups

#### Population 1 - titanium-based medialized cortical bone trajectory (mPACT)

Cortical bone trajectory, medial-to-lateral, pedicle screws are placed under fluororadiographic guidance. It is performed by identifying the uppermost lateral edge of the pars and moving 3 to 5 mm medial to identify the screw entry point. For the cephalad screw, it is important to avoid the adjacent facet capsule and set the entry point slightly inferior. Typically, the screw is placed with an approximately 15° medial-to-lateral trajectory and an approximately 30° interior-to-superior trajectory for the cephalad screw with a less steep trajectory for the caudal screw, limiting the surgical exposure required [21, 22] (Fig. 2). Decompression is added if necessary. The standard approach to the disc space can be attained via a posterolateral transforaminal (TLIF) route. Then poly-ether-ether-ketone (PEEK) or titan cages filled with bone of the decompression side are used [23, 24].

**Fig. 2 Fig2:**
[figure not shown]
The medialized cortical bone trajectory (mPACT) in comparison to the conventional pedicle srew instrumentation

#### Population 2 - conventional titanium-based instrumentation

The control group needs to represent the gold standard of care and is represented by rigid interbody fusion with titanium-based pedicle screw instrumentation (Fig. 2) [25].

### Randomization

Randomization should avoid selection bias for each group. The allocation ratio is 1:1. Allocation of treatments will be performed using a computer-generated list. Statistical Software Stata 10.0 module Ralloc version 3.5.2 (Statacorp College Station, TX, USA) will be used to generate the random code (CODE: ralloc block size treat, ratio(1) osiz(2) nsubj(77) trtlab(mPACT konventionell) strata(2) seed(20161012) sav(*File-Path*) idvar(study_ID)). An independent statistician at the Department of Medical Statistics, Informatics and Health Economics, Innsbruck Medical University will administer the randomization code (Fig. 3).

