## Methods/design

### Study design

The mPACT study is a single-center, randomized, controlled, parallel group, superiority trial with 154 patients allocated to the groups in a 1:1 ratio. Any trial involving a surgical procedure precludes surgical investigators from being blinded. Patients, however, will be blinded to the randomized treatment and further evaluations, such as radiologic analyses, will be conducted in a blinded fashion whenever possible. The expected enrollment time is 2 years. The conclusion of the study is estimated 5 years thereafter. The primary study endpoint is the difference in Oswestry Disability Index (ODI) between treatment groups at 2 years after surgery. The ODI is a widely used tool for the assessment of therapeutic effect. It consists of ten sections, with six questions in each section. A lower score indicates a higher level of function. An overall score of all 10 sections of the ODI will be computed and used as the ODI score. The standardized version of the ODI can be computed by re-scaling the score to the range 0–100 [8]. Moreover, the generic health status is assessed with the EuroQoL 5-Dimension questionnaire (EQ-5D) [9]. The Beck Depression Inventory (BDI) is used as a multiple choice self-reported inventory for measuring the severity of depression and responsiveness to treatment [10]. To identify neuropathic pain components the painDETECT questionnaire (PD-Q) will be used [11]. Furthermore, with the “timed up and go” (TUG) test the physical ability of walking is objectively documented and quantified [12]. Preoperative and postoperative magnetic resonance imaging (MRI) of the lumbar spine is performed. The image protocols include sagittal and axial sequences, both T1 and T2 weighted, in all patients [13–17]. A computed tomography (CT) scan is routinely performed one year after the intervention to assess the overall fusion rate [18]. Pre-operative American Society of Anesthesiologists (ASA) grade staging might allow the identification of risk factors. Neurological status and the quality and quantity of current pain medication are documented. Operation time and time of hospitalization is recorded. Pain medication usage, including epidural injections and nerve block injections are documented. Quantitative sensory testing (QST) is performed to assess and quantify low back pain non-invasively [19]. Blood samples will be tested preoperatively and postoperatively for TNF-α, IL-6, C-reactive protein (CRP) and leukocytes [20]. Direct costs of hospital care and the indirect costs of follow-up treatment outside the hospital will be evaluated. Costs of surgery and hospitalization including duration of inpatient stay, costs of nursing, costs of medication and physiotherapy are assessed after discharge from the hospital, according to the hospital’s internal cost-estimate lists. Additionally, the indirect costs after hospital discharge including physiotherapy, rehabilitation centers, pain medications, medical consulting etc. are documented on a routing sheet. Postoperative care is not standardized in the study protocol and will be performed according to the standard of care for degenerative lumbar spondylolisthesis at the study site. Primary and secondary outcome parameters are outlined in more detail in Table 1. Ethics approval was attained at the local ethics committee. This study complies with the World Medical Association Declaration of Helsinki Ethical Principles for Medical Research Involving Human Subjects, 2008. The final report will follow the CONSORT 2010 guidelines and its extension to non-pharmacological interventions. The CONSORT checklist is attached as Additional file 1.

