### Selection bias

Selection bias should be avoided by the randomization of the allocated intervention. All patients accomplishing the inclusion criteria are considered for participation and pre-screening lists are kept to justify non-included patients. Performance bias should be avoided by a standardized protocol of postoperative care at our department. Both groups receive the same preopeative and postoperative treatment until discharge. Attrition bias should be avoided by the “intention-to-treat” or “per-protocol” analysis, respectively. Every patient included in the trial will be considered in the overall evaluation.

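### The printed randomization command implies very short permuted blocks; in a single-center trial with unblinded surgeons, a recruiter who tracks assignments could guess up to about 72–75% of them

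*Protocol article*

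**What the plan says.** All references are to the protocol article.

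- **Randomization** prints the list-generating command, including "ralloc block size treat, ratio(1) osiz(2) nsubj(77) trtlab(mPACT konventionell) strata(2" (closing bracket follows). It states that "The allocation ratio is 1:1" and that an independent statistician "will administer the randomization code". No block length is given in words, and osiz is not explained. The same section gives the aim: "Randomization should avoid selection bias for each group".
- **Study design** describes a "single-center, randomized, controlled, parallel group, superiority trial with 154 patients allocated to the groups in a 1:1 ratio" and says: "Any trial involving a surgical procedure precludes surgical investigators from being blinded".
- **Selection bias** relies on the same safeguard: "Selection bias should be avoided by the randomization of the allocated intervention". It adds that lists of pre-screened patients are kept to account for those not included.

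**The concern.** In permuted blocks, the arm that is behind in the current block is the likelier next assignment. The shorter the block, the stronger that signal. An independent list holder hides the list, but not the running count from people who see which operation each patient received.

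The article gives recruiters both room and possible motive to act on a guess. Eligibility includes judgements: whether conservative therapy has failed, whether imaging matches the symptoms, and whether other surgery is foreseeable within 6 months (Study population, Table 2). The Background says that use of the technique depends mainly on the surgeon's own preference and skill. A recruiter who expects a particular arm could enroll, defer or exclude a patient accordingly. Blinding the patients does not prevent this, and the 2-year ODI comparison could then reflect who was enrolled under each guess.

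**Working it through.** **Inputs.** Two arms, 1:1, osiz(2), nsubj(77), strata(2) (Randomization); 154 patients, one center, unblinded surgeons (Study design); ODI standard deviation 20 (Sample size and power calculation). The article gives no predictability figure to reproduce. Its list length does reproduce: 77 × 2 = 154, so the command is read as two strata of 77.

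**Assumptions.** The guesser sees past assignments in order within each stratum, names the arm with fewer patients so far, and tosses a coin when the count is level. For the two-sizes reading, the sizes are taken as 2 and 4, equally likely.

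**1. Correct guesses.** For block size 2b, the expected share is [b + 2^(2b−1)/C(2b,b) − 1/2] / (2b).

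- Size 2: (1 + 2/2 − 0.5)/2 = 0.750
- Size 4: (2 + 8/6 − 0.5)/4 = 0.708
- 2/4 mix, weighted by length: (2 × 0.750 + 4 × 0.708)/6 = 0.722

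Simulated lists of 77 gave 0.747, 0.706 and 0.719.

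**2. Certain assignments** (guesser knows the possible block sizes).

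- Blocks of 2: every second assignment, 38/77 = 49%.
- 2/4 mix: certainty arises only when a block of 4 opens with two of the same arm (probability 2/6); its last two assignments are then fixed. With mean block length 3, the share is 0.5 × (1/3) × 2 / 3 = 0.111; simulated 0.109.

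In the 2/4 mix the count is off balance for (0.5 × 1 + 0.5 × 2.333)/3 = 56% of assignments (simulated 55%). There the guess is right on average (0.722 − 0.5 × 0.444)/0.556 = 90% of the time.

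**3. Illustrative bias.** Suppose patients enrolled when one arm is expected have an expected ODI d points higher, and d points lower when the other is expected. With c the share of correct guesses, the false difference between arms is 2d(2c − 1). For the 2/4 mix this is 2d(2 × 0.719 − 1) = 0.876d. With all 154 patients the standard error is 20 × √(2/77) = 3.22. Type I error is for a two-sided 0.05 two-group t test.

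| Assumed d | False difference (points) | Type I error, formula | Type I error, simulated |
|---|---|---|---|
| 0 | 0 | 5% | 5% |
| 1 | 0.88 | 5.8% | about 6% |
| 2.5 | 2.19 | 10.4% | about 11% |
| 5 | 4.38 | 27.1% | about 27% |

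**4. Alternatives, same simulation.**

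| Scheme | Correct guesses | Certain or forced | Type I error, d = 2.5 / 5 |
|---|---|---|---|
| Blocks of 2 | 75% | 49% | 12% / 33% |
| 2/4 mix | 72% | 11% | 11% / 27% |
| Blocks 2 to 10, weights 1:4:6:4:1 | 68% | 0.3% | 8% / 19% (formula, c = 0.677) |
| Imbalance limit 4 per stratum | 56% | 12% | 5% / 6% |

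**The case against.** - **The option is undefined.** A reader might infer that every block has size 2. The article does not support that: the command names a separate size variable, which fits varying block sizes at least as well. This stands, and it matters, because the certain share is 49% on one reading and about 11% on the other. The share of correct guesses barely depends on the reading.
- **Unblinded does not mean fully informed.** A reader might infer that surgeons know every earlier assignment in order. The article says only that they cannot be blinded. There are two sequences to track, the stratification factor is not named in the text available, and the randomization figure is not shown. This stands: 72–75% is an upper figure.
- **Safeguards exist.** The independent statistician conceals the list. The pre-screening lists record exclusions, though they do not prevent a deferral or a judgement-based exclusion. The Statistical analysis section allows baseline covariates, which could absorb part of any steering on baseline severity; the illustration uses an unadjusted test. These reduce the problem without removing it.
- **The steering is assumed.** Nothing in the article supports a shift of 2.5 or 5 points, and with no steering the error stays at 5%. This stands: 11% or 27% must not be read as the trial's actual error rate.
- **The alternatives are imperfect.** The imbalance limit forces about 12% of assignments, no better than the certain share in a 2/4 mix; its gain is in overall guessing. Blocks of 2 to 10 lower correct guesses only from 72% to 68%.

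**Conclusion.** The concern holds in a limited form. On either reading of osiz(2) the blocks are very short, and someone tracking assignments by stratum could guess up to about 72–75%, with 11% to 49% certain. That contradicts the reliance on randomization alone to keep selection bias out. The figures assume two strata of 77, full tracking and, for the second reading, an equal mix of 2 and 4.

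The article gives no evidence that steering occurs, so the ODI bias cannot be stated, only illustrated. The printed seed is a separate matter: a new, unpublished seed with the same block option would leave this weakness in place.

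**What to change.** For patients not yet randomized, the same independent statistician should generate a new list. Two options:

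- **At the least:** more and larger block sizes in random order, for example 2 to 10 (about 68% correct guesses, under 1% certain).
- **For a larger gain:** a list restricted only by a maximum imbalance, for example 4 per stratum (about 56% correct guesses, about 12% forced at the limit).

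The statistician should record what osiz(2) meant and what replaces it, and keep the new parameters from recruiting surgeons until enrollment ends. On the article's schedule (start January 2017, 2 years' enrollment, publication February 2018), patients would still have remained to be randomized.

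The cost is a short amendment and slightly less exact balance, with no extra patients. With the limit of 4, the simulated final difference between arms averaged 2.5 patients and never exceeded 6 of 154. Even an 80/74 split barely changes precision: (1/80 + 1/74)/(2/77) = 1.0015, so the standard error rises by less than 0.1%.

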### Trial status

The trial will start in January 2017 at the Department of Neurosurgery, Medical University of Innsbruck.

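### The randomization command and its seed were published inside the planned recruitment window, so allocation concealment cannot be assured for patients allocated after publication

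*Protocol article*

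**What the plan says.** The Randomization section of the protocol article names the software, "Statistical Software Stata 10.0 module Ralloc version 3.5.2", and says that it "will be used to generate the random code". It then prints the command, including "ratio(1) osiz(2) nsubj(77) trtlab(mPACT konventionell) strata(2) seed(20161012". Only the file path for saving the list is replaced by a placeholder. The one safeguard in that section's text is that an independent statistician at the university's statistics department "will administer the randomization code". Fig. 3 (Randomization) is not shown.

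The dates come from three places. The article header gives publication on 20 February 2018. Trial status says: "The trial will start in January 2017". Study design says: "The expected enrollment time is 2 years".

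On blinding, Study design says: "Any trial involving a surgical procedure precludes surgical investigators from being blinded". It adds that patients are blinded. The Selection bias section relies on the random allocation: "Selection bias should be avoided by the randomization of the allocated intervention". It also says that pre-screening lists are kept to account for patients who are not included.

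**The concern.** A seeded generator with fixed options returns the same sequence each time. Whoever holds the command and seed can produce the list and read off each coming assignment. Having an independent statistician administer the list protects it only while others cannot recreate it.

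The risk lies at entry to the trial. At a single center the surgeons know which procedure each patient received. Eligibility leaves room for judgement, for example on a patient's psychosocial ability to follow the protocol, or on whether other surgery is likely within six months. Someone who knows the next arm can influence who is enrolled and when. Blinding the patient does not prevent this, because the selection happens before allocation. Analysis as randomized does not repair it either, because the arms would already differ in prognosis. The protection claimed in the Selection bias section would then be open to question for the affected patients.

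This is not a complaint about something that an article leaves to the full protocol. It concerns what the article discloses.

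**Working it through.** **1. Is the printed command the live one?** The text presents it as the command that will generate the code. It nowhere calls the seed a dummy or says that it was replaced. If the options are read as 77 subjects in each of two strata, 77 × 2 = 154, the trial's total. The seed also reads as a date, 12 October 2016, shortly before registration on 3 November 2016. Both points are inference, but both fit a live command.

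**2. Is the list reproducible?** Software version, module version, ratio, osiz, number of subjects, strata, labels and seed are all printed. A generic seeded block generator run twice with this seed gave the same 77 entries both times. With the seed raised by one, only 34% of positions agreed with the first list. This illustrates the principle. The trial's own list was not regenerated, because Stata and the module were not available. The text does not name the stratification factor, so an outsider would not know which list belongs to which stratum. Site staff could probably match them from assignments already made.

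**3. How much of recruitment lay after publication?** Inputs: start between 1 and 31 January 2017, duration 2 years (730 days), publication on 20 February 2018, N = 154. Fraction remaining = 1 − (days elapsed ÷ 730).

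- Start 1 January 2017: 415 days elapsed (56.8%). Remaining 315 ÷ 730 = 43.2%; 154 × 0.432 = 66.5 patients.
- Start 31 January 2017: 385 days elapsed (52.7%). Remaining 345 ÷ 730 = 47.3%; 154 × 0.473 = 72.8 patients.

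Rounded up to whole patients, 67 to 73 were still to be allocated, if accrual was uniform and on plan.

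**4. What can a before/after comparison detect?** Take about 43 patients per arm before publication and 34 after, the planned SD of 20 ODI points, and no dropout. The between-period difference in treatment effect has

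SE = 20 × √(2/43 + 2/34) = 20 × √0.1053 ≈ 6.5 points.

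The difference detectable with 80% power at two-sided 0.05 is (1.96 + 0.84) × 6.5 ≈ 18 points. This exceeds the 10-point difference for which the trial is sized, and dropout would make it larger. Such a comparison can expose gross steering but cannot show that there was none.

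**The case against.** The strongest reply is that a list that could be regenerated is not a list that was regenerated. That stands. A reader might infer that concealment was in fact lost, or that patients were steered. The documents support only the weaker statement that concealment can no longer be assured.

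Other points on this side:

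- **Dates.** The window rests on planned dates and an expected enrolment time; actual accrual is not given. This stands, so the 43% to 47% is a scenario.
- **Earlier exposure.** Because Trial status is written in the future tense, a reader might infer that investigators had the command before the first patient and that all 154 allocations were exposed. The text does not say who saw the command or when, so this is not supported.
- **Short blocks.** A reader might argue that the blocks alone make assignments guessable. For assumed block sizes of 2, 2/4, 4 or 4/6, guessing the under-represented arm is right about 69% to 75% of the time, against 50% under simple randomization. But the article does not explain osiz(2), so the sizes are assumption. The point does not need them, because the seed fixes every slot.
- **Size of bias.** Any figure in ODI points needs an assumed prognostic shift that the documents do not supply. None is claimed here.
- **Safeguards.** Patient blinding limits bias in reporting the ODI, which is a separate matter from selection at entry. Pre-screening lists make selective exclusion auditable, but they do not prevent steering by timing.
- **Unnamed strata and Fig. 3.** The unnamed strata make it harder to use the list, probably not by much for site staff. Fig. 3 may describe the assignment procedure, so nothing is concluded from its absence.

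None of this answers the core: the command and seed are in print, dated inside the planned recruitment window, and no passage says that they were replaced.

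**Conclusion.** The point holds in this form: from 20 February 2018, allocation concealment from the unblinded surgeons can no longer be assured, because the published command and seed allow the list to be regenerated. It rests on three things: the printed command being the one in use, as the text says; enrolment still being open at publication, as the planned dates imply; and the strata being matched to their lists, which is probable for site staff. Under uniform accrual on plan, 67 to 73 of 154 patients (43% to 47%) are affected. The documents show neither actual selection nor its direction or size, and they give no ground for extending the exposure to patients allocated before publication. The exposure still needs correcting, because it touches the validity of the primary comparison, is cheap to stop, and cannot be undone for patients already allocated under the exposed list.

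**What to change.** 1. For every patient not yet randomized, the independent statistician generates a replacement list from a new, undisclosed seed and undisclosed block sizes.
2. Seed and block details stay out of public and investigator-facing documents until the last patient has been allocated.
3. Pre-specify a sensitivity comparison by arm of baseline ODI, number of levels and 2-year ODI, split at the publication date. Keep patients allocated between publication and the list change as their own group. A split at the list change alone would pool exposed patients with unexposed ones. State its low power, so that a null result is not read as reassurance.
4. If enrolment has closed, a new list is no longer possible. Report the comparison split at publication and state the limitation. If the printed seed was never the one in use, say so; that would settle the matter.

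The cost is small: a short amendment, a little of the statistician's time, two lists to document and one extra analysis. Treatments, endpoint and sample size do not change.

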**Fig. 3 Fig3:**
[figure not shown]
Randomization

### Selection bias

Selection bias should be avoided by the randomization of the allocated intervention. All patients accomplishing the inclusion criteria are considered for participation and pre-screening lists are kept to justify non-included patients. Performance bias should be avoided by a standardized protocol of postoperative care at our department. Both groups receive the same preopeative and postoperative treatment until discharge. Attrition bias should be avoided by the “intention-to-treat” or “per-protocol” analysis, respectively. Every patient included in the trial will be considered in the overall evaluation.

